#### Sample size and power considerations

We performed an a priori power analysis to determine the sufficient sample size for the stepped-wedge cluster RCT design, where the unit of randomization is the geographic area (cluster). Thus, there are two important sample estimates: N, for the number of mother/daughter dyads and K, for the number of LGAs. Specifically, the N participants will be nested within the K clusters. This nesting will likely create dependency on the data. The degree of this dependency depends on the intraclass correlation coefficient (ICC). The required sample size is calculated for the primary outcomes of HPV vaccination uptake for daughters and HPV self-collection uptake for mothers. Assuming a total of 18 LGAs with 34 dyads per LGA (N1 = 18 × 34 = 612 for daughters and N2 = 18 × 34 = 612 for mothers, total N = N1 + N2 = 1224), four total intervention periods, 2-sided alpha = 0.05 and 80% power, we calculated the minimum detectable rate of the primary outcome uptake at follow-up (Table 3 below). We expect three possible baseline rates of 0.10, 0.15, and 0.20 and compute the minimum detectable differences between the baseline and follow-up rates (hence minimum detectable follow-up rates) for the two primary study outcomes, assuming three possible ICC values of 0.005, 0.01, and 0.05. As shown in Table 1, the minimally detectable follow-up rates are much less than expected of the follow-up 50–60% self-collection uptake rates [67–69] and 65% HPV vaccination [11]. Hence, we have sufficient power (> 80%) to detect the increases in HPV vaccination among girls and HPV self-collection among their mothers after the implementation of the final crowdsourced campaign with a total of 18 clusters with 34 dyads per cluster (Table 3). To account for the 15% attrition rate at 6 months follow-up, we increased the sample size to 704 for mothers and daughters (40 dyads for each cluster). The calculation was performed using the software PASS 2019 (Power Analysis and Sample Size Software (2019) with the formulas developed by Hussey et al. [70]

**Table 3 Tab3:** Power and sample size for stepped-wedge RCT^a^

Cluster size (total sample size)	Rate of primary outcome at baseline (HPV self-collection uptake for mothers, HPV vaccination for daughters)								
	0.10^a^			^a^0.15			^a^0.20		
	ICC			ICC			ICC		
	0.005	0.01	0.05	0.005	0.01	0.05	0.005	0.01	0.05
	Minimally detectable rate of primary outcome at follow-up			Minimally detectable rate of primary outcome at follow-up			Minimally detectable rate of primary outcome at follow-up		
18(612)	^b^0.216	^b^0.220	^b^0.235	^b^0.283	^b^0.285	^b^0.300	^b^0.342	^b^0.346	^b^0.362

^a^Rate of primary outcome at baseline

^b^Minimum detectable rate of the primary outcome at follow-up composed of HPV prevention services uptake among intervention arm (2-sided test, 5% significance level, statistical power of 0.80)

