**Methods:**

A hybrid effectiveness-implementation type II pragmatic stepped-wedge cluster randomized control trial has been employed to the effectiveness of an implementation strategy bundle; a crowdsourced, tailored, community-engaged, mother-daughter HPV campaign on increasing uptake of HPV vaccination among girls aged 9–14 and HPV screening uptake among women aged 30–49 in Nigeria. The mother-daughter campaign will be tailored to local sites and conducted among 612 mother-daughter dyads (1,224 participants) recruited from 18 LGAs in six geopolitical zones of Nigeria. Trained community health workers will collect baseline data and implement a mother-daughter campaign that will provide education on cervical cancer control and access to onsite services for HPV vaccination and screening in a private area while engaging mothers and daughters simultaneously to increase uptake of the services. A mixed-methods evaluative and iterative assessment will be conducted using Proctor’s Implementation Outcomes Framework and the PEN- 3 cultural model. The primary outcomes are the uptake of HPV preventive measures—HPV vaccination (one dose) among girls (ascertained by onsite clinical records of vaccine uptake) and HPV self-collection completion among mothers (ascertained by laboratory receipt of self-collected specimens) within six months of trial enrollment. Pre-post effectiveness and cost of study components are embedded in the implementation and sustainment phases, compared to pre-implementation data assessed for each LGA.

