Mothers are female caregivers such as biological mothers, aunts, grandmothers, or guardians. We selected a pragmatic type II hybrid effectiveness design because it allows for a simultaneous assessment of the intervention implementation effectiveness and clinical outcomes assessment [39]. The study will be conducted among 612 mother-daughter dyads (*n* = 612 × 2 = 1,224 participants) recruited from 18 LGAs to a stepped-wedge randomized control trial of the crowdsourced intervention versus usual care. All mother-daughter dyads will be followed for 12 months. The Proctor’s Implementation Outcomes Framework [41] and the PEN- 3 cultural model [42] will guide the analysis and evaluation of the implementation process. We will recruit and train one CHW per LGA (*n* = 18) with one supervisor per LGA (n = 18) to assist with overall study implementation. Before participant recruitment, all CHWs will receive training on the final intervention, good clinical practice and human subject research. CHWs are key partners [43] that will recruit mother-daughter dyads meeting the eligibility criteria, identify barriers to engagement and participation, tailor and adapt the mother-daughter campaign to include access to onsite services for HPV self-collection kits, screen mothers and vaccination of girls by study nurses. CHWs will transport self-collected cervical samples to the NIMR laboratory, provide test results, link mothers to treatment for positive test results and retain participants overtime to advance efforts to eliminate cervical cancer in their LGAs. The trial is designed as a pragmatic study to closely mirror real-world conditions for on-going HPV prevention services in Nigeria.

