#### Recruitment

We will enroll mother-daughter dyads in the 18 LGAS. Recruitment methods include in-person events and venue-based, participant referral, community, religious setting and school-based referrals, social media, and online referrals. First, mother-daughter dyads will be identified and recruited to participate in an upcoming Mother-Daughter Day event on HPV prevention methods. Second, those who agree to participate will receive reminder text messages before the event. Third, trained CHWs and supervisors will provide educational information and materials on cervical cancer control at the event.

Fourth, onsite services for HPV vaccination and self-collection kits will be offered to mother-daughter dyads, with girls receiving HPV vaccinations immediately in an onsite vaccination dedicated private space designated for the mother-daughter Day event. Mothers will receive instructions on self-collection in a private area, and their samples will be returned to the NIMR laboratory. Trained CHWs will provide the results of the samples, and those with positive results will be linked immediately to the supervisors for treatment and follow-up care, which we will track overtime. A baseline survey will be conducted among 612 mother/daughter dyads (*n* = 1,224 total) recruited in 18 LGAs (capped at 34 per area). We will define mothers as any female caregiver, including biological and surrogate mothers or close relatives who meet eligibility criteria. Eligibility criteria for mother-daughter dyads are outlined in Table 1. Trained community healthcare workers will approach and obtain consent from participants in a private space. Parental mobile phone numbers will be collected as tracking information for follow-up and retention.

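### The attrition-adjusted sample size of 704 is miscalculated, does not equal 40 dyads in each of 18 LGAs, and is cancelled by a recruitment cap of 34 per LGA

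*Protocol article*

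**What the plan says.** In the protocol article, the section Sample size and power considerations starts from the unadjusted size: "Assuming a total of 18 LGAs with 34 dyads per LGA (N1 = 18 × 34 = 612 for daughters", and the same number for mothers. Table 3 and the claim of more than 80% power are both tied to 34 dyads in each of 18 clusters. The section then allows for 15% attrition at 6 months: "we increased the sample size to 704 for mothers and daughters (40 dyads for each cluster".

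Elsewhere the unadjusted number is the enrolment number. The Recruitment section places the baseline survey in 612 dyads "recruited in 18 LGAs (capped at 34 per area". The Methods section says "The study will be conducted among 612 mother-daughter dyads". The abstract has the campaign "conducted among 612 mother-daughter dyads (1,224 participants) recruited from 18 LGAs". The end of the Introduction also gives 612. Neither 704 nor 40 per LGA appears outside the sample size section.

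**The concern.** There are two faults.

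- **The adjusted total.** The sentence gives a total and a per-cluster figure that do not agree, and the total is too small for the attrition it is meant to absorb.
- **The recruitment rule.** The cap and the enrolment statements use the number from before the adjustment, so the protection against attrition exists only in the sample size section.

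An LGA team that follows the Recruitment section stops at 34 dyads; one that follows the sample size section goes on to 40. If recruitment stops at 34, the trial analyses fewer dyads than Table 3 assumes. Planned enrolment is also the number against which recruitment and completion will be judged, and here it can be read as 612, 704 or 720.

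**Working it through.** **Inputs, all from the section Sample size and power considerations unless noted.** 18 LGAs; 34 dyads per LGA (612); 15% attrition; adjusted size given as 704 and as 40 per LGA; "four total intervention periods, 2-sided alpha = 0.05 and 80% power"; "We expect three possible baseline rates of 0.10, 0.15, and 0.20"; "assuming three possible ICC values of 0.005, 0.01, and 0.05". Cap of 34 per LGA from the Recruitment section.

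**Step 1: where 704 comes from.** 612 × (1 + 0.15) = 703.8, which rounds to 704. This adds 15% to the target instead of dividing by the retained fraction.

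**Step 2: what is needed.** n/(1 − d) = 612/0.85 = 720, and 720/18 = 40 per LGA. The per-cluster figure therefore matches the right formula and the total does not: 704/18 = 39.1.

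**Step 3: dyads left after 15% loss.**

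| Enrolled | Per LGA | Retained | Retained per LGA | Short of 612 |
|---|---|---|---|---|
| 720 | 40 | 612.0 | 34.0 | 0 |
| 704 | 39.1 | 598.4 | 33.2 | 14 |
| 612 (the cap) | 34 | 520.2 | 28.9 | 92 (15%) |

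**Step 4: reproduce Table 3.** The protocol cites the Hussey–Hughes method. Its variance for the intervention effect is

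Var = Iσ²(σ² + Tτ²) / [(IU − W)σ² + (U² + ITU − TW − IV)τ²],

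with I = 18 clusters and T = 5 periods (one control period plus four steps). Here σ² is the mean of the two binomial variances divided by the dyads per cluster-period, and τ² is that mean variance × ICC/(1 − ICC). The article does not give the wave sizes or the dyads per period. I assumed waves of 5, 4, 4 and 5 LGAs and 34/5 = 6.8 dyads per cluster-period. Then U = 45, W = 599 and V = 137. The minimum detectable rate p₂ solves (p₂ − p₁)/√Var = 1.96 + 0.84.

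| Baseline | ICC | Table 3 | Reproduced, 34 per LGA | 28.9 per LGA |
|---|---|---|---|---|
| 0.10 | 0.005 | 0.216 | 0.217 | 0.227 |
| 0.10 | 0.01 | 0.220 | 0.220 | 0.231 |
| 0.10 | 0.05 | 0.235 | 0.235 | 0.246 |
| 0.15 | 0.005 | 0.283 | 0.281 | 0.293 |
| 0.15 | 0.01 | 0.285 | 0.285 | 0.297 |
| 0.15 | 0.05 | 0.300 | 0.301 | 0.313 |
| 0.20 | 0.005 | 0.342 | 0.342 | 0.354 |
| 0.20 | 0.01 | 0.346 | 0.346 | 0.358 |
| 0.20 | 0.05 | 0.362 | 0.362 | 0.375 |

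The reproduction is within 0.002 of every cell, so Table 3 does rest on 34 analysed dyads per LGA. At 28.9 per LGA the detectable rates rise by about 0.011 to 0.013.

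**Step 5: power at the rates printed in Table 3, same model.**

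- 34 per LGA: 0.80 to 0.81
- 33.2 per LGA (704 enrolled): 0.79 to 0.80
- 28.9 per LGA (612 enrolled): 0.73 to 0.75

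**Step 6: power at the expected rates.** The protocol expects 50–60% self-collection and 65% vaccination. The hardest of these contrasts is 0.20 to 0.50 at ICC 0.05. With 28.9 dyads per LGA its power is 0.997.

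**The case against.** The strongest reply is that the error changes no conclusion about power. The protocol argues that the Table 3 limits lie far below the uptake it expects, and with 28.9 dyads per LGA that remains true: the worst limit moves from 0.362 to about 0.375, well under 0.50. This stands. The point should not be read as saying that the trial is underpowered for its planned effect.

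A second reply is that 704/18 = 39.1 may simply have been rounded up to 40 whole dyads per cluster, and 40 is adequate. That reading rescues the per-cluster figure, but the total is then 720 and 704 is still wrong. The slip between 704 and 720 is small in itself: 16 dyads, and less than one point of power after attrition.

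A third reply is that the figure of 28.9 is a worst case. The outcomes come from onsite vaccination records and laboratory receipt of specimens, services are offered at the event, and the planned mixed model uses partial follow-up. Some dyads lost later would still contribute. This also stands, and it limits the size of the power loss. It does not settle which enrolment target applies.

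Finally, 612 could be taken as the number expected after attrition. The text does not allow this, because the Recruitment section attaches 612 and the cap to the baseline survey, before any loss.

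**Conclusion.** The concern holds. The total of 704 is wrong for 15% attrition and disagrees with 40 per LGA in its own sentence; the consistent figure is 720. The recruitment cap of 34 and the repeated enrolment figure of 612 cancel the adjustment altogether, and this contradiction between 34 and 40 per LGA is the part that matters.

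Under the cap, about 520 dyads remain, 92 fewer than Table 3 assumes. Power at the printed detectable rates falls to about 0.74, and those rates rise by about 0.011 to 0.013. The counts follow by arithmetic alone. The power figures assume five periods with equal dyads in each, waves of 5, 4, 4 and 5, and no outcome data from lost dyads; other splits of the 18 LGAs into waves move the detectable rates by up to about 0.006. Power for the uptake the protocol expects is not threatened.

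**What to change.** Choose one enrolment figure and use it throughout.

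- **Option A: apply the adjustment.** Replace 704 with 720 dyads (1,440 participants, 40 per LGA). Raise the cap in the Recruitment section to 40, and align the 612 and 1,224 enrolment statements in the abstract, Introduction, Methods and Recruitment. Table 3 then stands, since 720 × 0.85 = 612. The cost is 720 − 612 = 108 more dyads (216 participants, about 18% more), with the vaccines, kits and laboratory work that go with them.
- **Option B: keep 612 enrolled.** Delete the sentence giving 704 and 40 per cluster, recompute Table 3 for about 29 analysed dyads per LGA, and say that the limits still lie well below the expected uptake. This enrols no one extra and costs only text edits and slightly less favourable detectable rates.

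Under either option, state the wave sizes and the dyads per period used in the power calculation, so that Table 3 can be reproduced without assumptions.

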### Statistical analysis

#### Data analysis

The primary analyses will examine rates of HPV self-collection (mothers) and single-dose vaccine receipt (daughters). Analyses will be performed separately for the mother sample and daughter samples. The main analyses will compare the rates of HPV self-collection (mothers) and vaccine uptake during the pre-and post-intervention periods. We will examine a hypothesis comparing the superiority of the intervention with pre-intervention periods using the stepped-wedge cluster randomized control design and account for any temporal changes in HPV vaccination or screening rates during the 6-month conduct of the trial. This analysis will be accomplished with generalized linear mixed models to account for the within-person factor – time (baseline, 3 months, and 6 months) and one primary between-person factor (randomization site dummy code as 0 = convention and 1 = intervention). The 3-level model is structured as observations nested within subjects within local government areas. Multilevel modeling software (SAS, version 9.4, PROC GLIMMIX with logit as link function) will be used to compute full information maximum likelihood (FIML) estimates of the model parameters. The model will include intervention status and time as fixed effects and site and individuals as random effects. The estimated intervention effects will be reported with 95% CIs and p values. Secondary analyses will explore linkage rates to clinical follow-up after positive HPV testing in pre-intervention and post-intervention periods.

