#### Randomization and rationale for stepped-wedge design

The 18 LGAs will be randomly allocated to the intervention, 4–5 LGAs per month for 12 months. All sites begin as part of the control condition and are block-randomized into four waves, with each wave beginning two months after the start of the prior wave and lasting for 6 months, followed by a 6-month follow-up period. All clusters will eventually receive the intervention, with outcomes measured every three months across all clusters. See Fig. 2for a schematic of the stepped-wedge cluster RCT design. Randomization will be conducted by the study statistician, who will not have direct contact with the LGAs. All LGAs will be informed of their assigned intervention wave before the first wave begins. Blinding was not implemented in this study, as all sites will eventually receive intervention, reflecting typical conditions in real-world settings. The stepped-wedge design was deemed acceptable and ethical by key program partners (NIMR and the Nigerian Ministry of Health) and study collaborators for logistical and pragmatic reasons, given the potential benefits of the intervention package (i.e., combined cervical cancer prevention strategies of vaccination and screening) and the equitable provision of the intervention to all sites [40].

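### The primary mixed model is defined in terms that contradict the stepped-wedge rollout, and its person random intercept does not suit a once-only outcome

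*Protocol article*

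**What the plan says.** The protocol article describes the design and the analysis in different terms.

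- **Design** (Randomization and rationale for stepped-wedge design). All LGAs start in control and are block-randomised to four waves. Waves start two months apart, each lasts 6 months, and a 6-month follow-up comes after. "All clusters will eventually receive the intervention, with outcomes measured every three months across all clusters".
- **Intervention term** (Data analysis). There is "one primary between-person factor (randomization site dummy code as 0 = convention and 1 = intervention". The same paragraph also lists intervention status and time as fixed effects and describes a comparison of pre- and post-intervention periods.
- **Time term** (Data analysis). Time is a within-person factor at baseline, 3 and 6 months, and the analysis is to "account for any temporal changes in HPV vaccination or screening rates during the 6-month conduct of the trial".
- **Random effects and estimation** (Data analysis). "The 3-level model is structured as observations nested within subjects within local government areas". Site and individual are random, the link is logit, and estimation is by full-information maximum likelihood.
- **Outcome** (Outcomes; Table 4). The outcomes are one vaccine dose and one completed self-collection, each within 6 months of enrolment. Table 4 tabulates both as proportions at baseline, 3 and 6 months. How a person is coded after the event is not stated.

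**The concern.** In a stepped wedge the effect is identified because LGAs switch condition at different calendar times. The model must therefore carry a status that changes within each LGA and a time term that follows the calendar across all the steps. A between-person site dummy and a 6-month time scale provide neither. Calendar time matters here because the Introduction and Setting describe a national vaccine rollout already under way, which could raise uptake with or without the campaign.

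The second issue is the outcome. A girl vaccinated once stays vaccinated. A person random intercept is meant for outcomes that can go up and down within a person, and on cumulative once-only status it can break the estimation. At stake are the effect estimates and confidence intervals for both primary outcomes.

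**Working it through.** **1. The plan's own power figures.** Inputs from Sample size and power considerations: "2-sided alpha = 0.05 and 80% power"; "Assuming a total of 18 LGAs with 34 dyads per LGA"; "four total intervention periods"; "We expect three possible baseline rates of 0.10, 0.15, and 0.20"; ICC 0.005, 0.01, 0.05. Table 3 is closely matched by the Hussey-Hughes variance with I = 18 LGAs crossing over 5/5/4/4, T = 5 periods and 34/5 = 6.8 different people per LGA-period:

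Var = Iσ²(σ² + Tτ²) / [(IU − W)σ² + (U² + ITU − TW − IV)τ²], with U = 47, W = 645, V = 145.

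Example with rates 0.10 and 0.216 and ICC 0.005:
- Mean variance = (0.0900 + 0.1693)/2 = 0.1297; σ² = 0.1297 × 0.995/6.8 = 0.01897; τ² = 0.1297 × 0.005 = 0.00065.
- Var = 0.00759/(201 × 0.01897 + 604 × 0.00065) = 0.00180; SE = 0.0425.
- Power = Φ(0.116/0.0425 − 1.96) = 0.78.

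Across Table 3, power at the stated rates is 0.78 to 0.81. The recomputed detectable rates (0.219/0.222/0.233, 0.284/0.287/0.299, 0.345/0.348/0.360) lie within about 0.003 of those stated. The best-fitting power model thus has five periods, different people in each and no person effect, which is not the model in Data analysis.

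**2. Is the intervention effect estimable?** Take the columns baseline (B), month 3 (M3), month 6 (M6) and intervention (X).
- Dummy constant per site, every LGA treated: X = 1 = B + M3 + M6. Rank 3 of 4, not estimable.
- Time counted from enrolment at the LGA's own campaign: X is 0, 1, 1 for everyone, so X = M3 + M6. Rank 3 of 4, aliased with time.
- Calendar months 0, 3, 6 with time-varying status: rank 4 of 4, estimable.

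**3. What calendar months 0, 3 and 6 cover.** With waves starting at months 0, 2, 4, 6, the last wave ends at month 6 + 6 = 12. The start of wave 1 relative to baseline is not stated, so both options are shown, counting a wave as crossed once its start has passed.

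| Wave starts (months) | Crossed by 3 | Crossed by 6 | Waves with no intervention data |
|---|---|---|---|
| 0, 2, 4, 6 | 50% | 75% | 1 |
| 2, 4, 6, 8 | 25% | 50% | 2 |

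**4. Person random intercept on cumulative status.** Each series is all zeros, zeros then ones, or all ones. As the person SD grows, the model approaches one latent value per person crossing a threshold, which fits such series ever better. Simulation: 612 people, waves of 170/170/136/136, time-varying status, three visits, no LGA effect. Assumed uptake is 10/13/16% in control and 45/55% (months 3 and 6) under intervention.

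| Person SD | logL | Intervention log OR |
|---|---|---|
| 0 | −888.9 | 2.20 |
| 5 | −631.8 | 6.78 |
| 10 | −611.7 | 12.36 |
| 20 | −606.1 | 23.94 |
| 40 | −605.2 | 47.47 |

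The likelihood keeps rising and the log OR grows with the SD. A Laplace approximation also rises throughout (−794.9 at SD 1 to −557.9 at SD 40). With a between-person dummy the log OR goes from 1.81 to 41.18. Two further set-ups, both with assumed monthly hazards of 3% and 9%, agree:
- Statuses at 3 and 6 months: −logL falls from 550.6 (SD 0.5) to 457.2 (SD 16), and the log OR rises from 0.86 to 7.94.
- Waves at months 2/4/6/8, three-monthly status to month 12: −logL falls from 1338.8 (SD 0) to 869.6 (SD 20), and the log OR rises from 0.51 to 2.61.

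**5. The other coding.** If the event is coded 1 only in the interval where it occurs, logL is highest at SD 0 (−698.2) and falls to −707.3 at 0.5 and −730.9 at 1. Estimates are finite and the person effect is empty. People who have had the event stay in the denominator, which attenuated the log OR modestly in simulation (1.12 against a true 1.20; 1.98 against 2.19). Keeping only at-risk rows gave 1.19 and 2.19.

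**The case against.** The same paragraph names intervention status and time as fixed effects, compares pre- and post-intervention periods and undertakes to allow for temporal change. Three-monthly measurement in all clusters also favours calendar time. On that reading the effect is estimable. This stands: a reader might infer that the plan contains no stepped-wedge model at all, but the documents show incompatible definitions of its terms, not a demonstrated aliased model.

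A between-person status would also make sense if different dyads were observed in each period, as the power figures suggest. But Data analysis specifies repeated observations on each subject, so this does not rescue the text as written.

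Three stronger inferences are tempting and not supported:
- *That the model never has a finite estimate.* This depends on cumulative coding, which is the natural reading of Table 4 but is not stated.
- *That the p-value is meaningless.* The growing log OR is largely a change of scale: divided by the SD it settles (23.94/20 = 1.20; 47.47/40 = 1.19). In a simulation with 3% and 9% hazards, the likelihood-ratio statistic at SD 4, 8, 16, 32 was 37.7, 35.8, 36.0, 36.0; with equal hazards of 5% it was 0.85, 0.61, 0.55, 0.55. Wald output was not examined.
- *That baseline uptake is zero for everyone.* Table 1 excludes only recent vaccination or screening, and the sample size section plans on baseline rates of 0.10 to 0.20. The result in step 4 does not need a zero baseline.

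Finally, LGA-by-period effects and small-sample corrections are commonly left to an analysis plan that is not shown. Their absence is not counted as an error.

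**Conclusion.** The concern holds in this form: the stated primary model contradicts the stated design and must be reconciled with it. The between-person coding and the 6-month time frame cannot describe a rollout of about 12 months in which every LGA switches. Two of the three readings leave the effect unestimable; the third is estimable but leaves one or two of four waves without intervention data by month 6. That range depends on when wave 1 starts, which is an assumption.

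The person random intercept is a separate defect. Under cumulative coding and maximum likelihood there is no finite maximum, and the reported odds ratio and CI would be unusable. The pattern was the same in three simulated set-ups, although the individual figures depend on assumed uptake rates. Under event-interval coding estimates are finite and the person effect does nothing. Under neither coding does it help.

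**What to change.** Rewrite the model paragraph so that it:
- defines intervention as a time-varying LGA-by-period status, and deletes the between-person coding;
- uses categorical calendar period covering every step, and deletes the 6-month trial length;
- drops the person random intercept and states how uptake is coded after the event;
- analyses either one 6-month outcome per person, which keeps the outcome as defined under Outcomes, or a discrete-time first-event model on person-periods still at risk;
- keeps an LGA random effect, preferably with LGA-by-period, and uses small-sample inference for 18 clusters.

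With one outcome per person, the text must also say how to classify someone whose 6-month window straddles the LGA's crossover.

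Both options gave finite estimates when tried. One record per person with five calendar periods gave a log OR of 1.68 (SE 0.30) on one simulated data set with 15% against 50% uptake, and leaves the Table 3 rates unchanged. A first-event model recovered a log hazard ratio of 1.09 (true value ln(9/3) = 1.10); under the null its mean was 0.01 with 6.7% rejections in 150 runs.

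The cost is rewritten analysis text and code, with no added participants or data. If the first-event model is chosen, 6-month risks must be derived from it.

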Nigeria has programs and infrastructure in place to support the combined implementation of HPV vaccination and HPV self-collection among mother-daughter dyads [3]. Recently, to immunize 16 million girls by 2025 with a single dose of HPV vaccine, Nigeria launched a nationwide rollout of HPV vaccination in October 2023 when 15 states plus the Federal Capital made HPV vaccination available to approximately 5.3 million girls in an initial phase [25]. Phase 2 launched in May 2024 and over seven million girls in 21 states were vaccinated [25]. HPV vaccination is classified as a best buy for non-communicable diseases and is considered a highly cost-effective and affordable intervention for cervical cancer prevention [26]. Likewise, the 2019 Nigerian Society of Obstetrics and Gynecology guidelines [27], as well as the Nigerian National Strategic Plan for cancer, recommend routine HPV screening for women by ages 30–65 years old, including the early detection of asymptomatic pre-cancerous lesions and prompt treatment to prevent cervical cancers [3, 28]. Nonetheless, attempts to implement HPV vaccination and HPV screening in real-world settings in Nigeria have focused on standalone interventions implemented separately with girls or women as with the national rollout of HPV vaccination. Few studies have investigated the strategies necessary to integrate both HPV vaccination and HPV screening with mother-daughter dyads simultaneously, despite the availability of evidence suggesting its feasibility [16, 29]. Combined HPV vaccination and screening have the potential to improve the adoption of cervical cancer prevention interventions [16]. Such an approach capitalizes on reciprocal learning between mothers and daughters and facilitates the mutual reinforcement of health prevention practices and behaviors [12, 30–32]. Notably, dyadic approaches align with many cultures where parents make important health decisions for young girls [33–35]. Given the high incidence and mortality rates of cervical cancer in Nigeria, efforts to equitably increase the uptake of HPV vaccination and HPV screening using culturally compelling strategies are needed.

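### The primary model lets LGAs differ in level but not in their change over time, so standard errors are too small if LGAs drift apart, materially so near ICC 0.05

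*Protocol article*

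**What the plan says.** The Data analysis section specifies a logit mixed model in PROC GLIMMIX, run separately for mothers and daughters. Its structure is stated: "The 3-level model is structured as observations nested within subjects within local government areas", and "The model will include intervention status and time as fixed effects and site and individuals as random effects". On estimation, the software "will be used to compute full information maximum likelihood (FIML) estimates of the model parameters"; on reporting, "The estimated intervention effects will be reported with 95% CIs and p values". The same section says that the analysis should account for temporal changes in uptake during the trial.

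The power calculation uses the same structure: one ICC per scenario (0.005, 0.01 or 0.05), no separate between-period correlation, and the Hussey formulas, which have a constant cluster intercept. Its inputs are "Assuming a total of 18 LGAs with 34 dyads per LGA" and "four total intervention periods, 2-sided alpha = 0.05 and 80% power".

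No LGA-by-period term, decaying correlation or robust variance appears.

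**The concern.** In a stepped wedge the effect is estimated largely from changes within each LGA as it crosses from control to intervention. A constant site intercept removes stable differences between LGAs, and the fixed time effect removes changes that all LGAs share. Nothing in the stated model represents an LGA moving up or down on its own between periods. The model treats such movement as independent noise in single observations, which averages out over the dyads in an LGA. In truth it is shared by all of them and does not average out.

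The result would be standard errors that are too small, 95% intervals that are too narrow and more than 5% false positives, for both primary outcomes. Because the article states the random-effects structure outright, this is a choice already made and not a detail left open.

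**Working it through.** **1. Reproducing Table 3.** Inputs from the sample-size section: 18 LGAs, 34 dyads each, two-sided 0.05, 80% power. I take 5 periods (baseline plus four steps), so 34/5 = 6.8 dyads per LGA-period, and waves of 5, 5, 4, 4. With X the 0/1 treatment indicator, U = ΣX = 47, W = Σ(period totals)² = 645 and V = Σ(LGA totals)² = 145. The constant-intercept variance is

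Var = Iσ²(σ² + Tτ²) / [(IU − W)σ² + (U² + ITU − TW − IV)τ²].

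For baseline 0.15, follow-up 0.300 and ICC 0.05:
- averaged binomial variance (0.1275 + 0.2100)/2 = 0.16875
- σ² = 0.16875 × 0.95/6.8 = 0.02358 and τ² = 0.16875 × 0.05 = 0.00844
- Var = 0.02791/(201 × 0.02358 + 604 × 0.00844) = 0.00284, so SE = 0.0533
- power = Φ(0.150/0.0533 − 1.96) = 0.80

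All nine cells of Table 3 come back within 0.004. The plan's own figure therefore rests on the constant-intercept structure.

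**2. Closed-form check of the planned structure.** Assumptions not in the protocol: 34 dyads per LGA followed over 5 periods, within-person correlation 0.5, and between-period correlation a fraction λ of the within-period one. Set total variance to 1 and ICC to 0.05. The part of an LGA-period mean that changes from period to period has variance

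0.05(1 − λ) + 0.95 × 0.5/34.

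- λ = 0.8: 0.0100 + 0.0140 = 0.0240
- λ = 0.5: 0.0250 + 0.0140 = 0.0390

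A model with only site and individual effects pools this into the observation-level residual. For λ = 0.8 the pooled residual is (0.475 × 2376 + 0.815 × 68)/2444 = 0.484, where 2376 = 33 × 4 × 18, 68 = 4 × 17 and 0.815 = 0.475 + 34 × 0.01. The model then uses 0.484/34 = 0.0142 in place of 0.0240. For λ = 0.5 it uses 0.499/34 = 0.0147 in place of 0.0390.

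The square roots of these ratios are 0.77 and 0.61. The full generalized-least-squares calculation gives a model SE of 0.78 and 0.62 of the true SE. Against a normal reference, type I error is 2[1 − Φ(1.96 × 0.776)] = 12.8% and 2[1 − Φ(1.96 × 0.622)] = 22.3%. At ICC 0.005 to 0.01 the same calculation gives 5.7 to 8.7%.

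**3. Simulation.** 2,000 null trials per setting, maximum likelihood, z reference, nominal 5%; the logit settings use a baseline rate of 0.15. Each cell shows type I error (%) at λ = 1 / 0.8 / 0.5.

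| Setting | ICC 0.005 | ICC 0.01 | ICC 0.05 |
|---|---|---|---|
| Logit, site only, 34 per LGA-period | 6.1 / 6.7 / 6.8 | 6.4 / 7.3 / 7.9 | 7.4 / 11.4 / 16.1 |
| Linear cohort, site + individual, 34 per LGA | 4.9 / 5.3 / 6.5 | 5.0 / 6.1 / 7.9 | 4.8 / 12.4 / 21.4 |
| Logit, site only, about 7 per LGA-period | 5.6 / 4.9 / 5.3 | 5.7 / 5.1 / 5.6 | 5.8 / 6.9 / 8.2 |

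A linear version on LGA-period means (1,200 trials, ICC 0.05, 34 per LGA-period) gave 9.6% at λ = 0.8 and 16.1% at λ = 0.5. With LGA-specific linear trends of logit SD 0.25, 0.5 and 0.75 in place of period noise (4,000 trials), the logit model gave 5.2, 5.9 and 6.9% at ICC 0.01, and 6.6, 7.3 and 8.6% at ICC 0.05.

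**4. What repairs it.** At ICC 0.05, a t reference on 16 degrees of freedom without a new random effect still gives 8.4 and 12.9% (logit) or 9.7 and 18.4% (cohort). Adding the LGA-by-period effect to the cohort model gives 4.3 to 5.8% with ML and z, and 2.5 to 3.5% with REML and t(16).

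**The case against.** The strongest reply is that the large figures need several things at once: the highest of the three ICCs, an assumed decay in correlation, and 34 dyads in every LGA-period. At the other two ICCs, or at the cell size that reproduces Table 3, the error is close to nominal. That stands. A reader might infer that any LGA-specific change spoils the p-values; the results above do not support this, since mild trends and low ICCs do little harm.

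The simulations also depart from the stated trial. The site-only version with 34 per LGA-period, read as separate samples, would need 34 × 5 × 18 = 3,060 dyads, not 612. The cohort version is linear where the plan has a logit link, and uses 5 periods where Data analysis lists three time points. This limits precision but not direction.

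A reader might also infer that normal-theory Wald tests on 18 clusters are part of the fault. The protocol names neither. The reference distribution and degrees of freedom can be left to the SAP, and that part alone is small: about 5 to 7% at λ = 1.

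Finally, the phased vaccine rollout ("Phase 2 launched in May 2024 and over seven million girls in 21 states were vaccinated") and the local tailoring of campaigns might be read as proof of LGA-by-period variation. They are not. The reported rollout launches coincided with the pilot work, concern daughters only and would mainly shift starting levels, which the site intercept absorbs. Tailoring suggests that the intervention effect differs between LGAs, which is a different term and adds nothing under the null. LGA-by-period variation is thus a risk left unprotected against, not something the protocol demonstrates.

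**Conclusion.** The point holds in a limited form. The stated model cannot represent LGA-specific change over time, and if such change occurs the standard errors of both primary effects are too small. The size depends on the assumed between-period ratio (0.5 to 0.8) and, for the cohort figures, on 5 periods and a within-person correlation of 0.5. It matters near ICC 0.05 with 34 dyads per LGA-period and is slight to modest elsewhere.

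The trial's main conclusion is probably not at risk. The plan says "We expect three possible baseline rates of 0.10, 0.15, and 0.20" and expects 50 to 65% at follow-up, against detectable rates of 21.6 to 36.2% in Table 3. Power at the Table 3 rates also barely moves under decaying correlation (0.78 to 0.80), because that calculation uses only 6.8 dyads per LGA-period. What is at stake is mainly whether the 95% intervals have the coverage they claim.

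**What to change.** Add an LGA-by-period random effect to the primary GLIMMIX model for each outcome, keeping the site and individual effects, with periods matching the fixed time effect. As a sensitivity check, report a permutation test that re-randomises LGAs to waves within the planned blocks. Leave the degrees-of-freedom method to the SAP: a t reference alone does not repair the problem, and t(16) with REML may be conservative.

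The change is a few lines of code and text. The price is wider intervals: the SE is about 1.05 to 1.14 times larger at ICC 0.005 to 0.01, and about 1.3 to 1.6 times at ICC 0.05, for ratios of 0.8 to 0.5. The repair was checked in a linear cohort model only, so convergence of the logit version should be tested on simulated data before the analysis is locked.
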